## Abstract

**Background:**

The effects of exposure to ultraviolet radiation are a significant concern in Australia which has one of the highest incidences of skin cancer in the world. Despite most skin cancers being preventable by encouraging consistent adoption of sun-protective behaviours, incidence rates are not decreasing. There is a dearth of research examining the factors involved in engaging in sun-protective behaviours. Further, online multi-behavioural theory-based interventions have yet to be explored fully as a medium for improving sun-protective behaviour in adults. This paper presents the study protocol of a randomised controlled trial of an online intervention based on the Theory of Planned Behaviour (TPB) that aims to improve sun safety among Australian adults.

**Methods/Design:**

Approximately 420 adults aged 18 and over and predominantly from Queensland, Australia, will be recruited and randomised to the intervention (n = 200), information only (n = 200) or the control group (n = 20). The intervention focuses on encouraging supportive attitudes and beliefs toward sun-protective behaviour, fostering perceptions of normative support for sun protection, and increasing perceptions of control/self-efficacy over sun protection. The intervention will be delivered online over a single session. Data will be collected immediately prior to the intervention (Time 1), immediately following the intervention (Time 1b), and one week (Time 2) and one month (Time 3) post-intervention. Primary outcomes are intentions to sun protect and sun-protective behaviour. Secondary outcomes are the participants’ attitudes toward sun protection, perceptions of normative support for sun protection (i.e. subjective norms, group norms, personal norms and image norms) and perceptions of control/self-efficacy toward sun protection.

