Computer-based interventions have been used to target behaviour change in a wide range of health issues over the last decade and provide a means of administering economical and easily accessible interactive health interventions which are far reaching within the population [13,34]. Research by Cugelman et al. [34] found that, compared with waitlists, online interventions have demonstrated moderate efficacy while, compared with print materials, they offer similar impacts but with the advantages of lower costs and broader reach. Further, research by Webb et al. [35] found that more extensive use of theory, and specifically online interventions based on the TPB, tended to have more substantial effects on behaviour. Despite their demonstrated efficacy in producing health behaviour change, online, multi-behavioural, theory-based interventions have yet to be explored fully as a medium to target adults’ sun-protective attitudes, beliefs, and sun-protective behaviour within the Australian context.

Limited research has examined the efficacy of online/web-based interventions in increasing a specific sun-protective behaviour (e.g., sunscreen use; [36]); however, there is a particular dearth of theory-based, online interventions targeting multiple sun-protective behaviours. We hypothesise that adults exposed to the online intervention will report an increase in positive sun-protective attitudes, normative support, and self-perceptions of control/self-efficacy, leading to increased sun protection intentions and behaviour, compared with participants in both an information only and control group (measurement only).

This paper presents the study protocol for an online intervention aimed at improving sun-protective behaviour in adults. The research will use an extended version of the TPB to develop and test the efficacy of an online sun-protective intervention derived from this approach. The intervention will target previously identified attitudes toward sun protection, normative influences, and barriers and motivators, as well as targeted aspects of personal choice/responsibility, and tanning being part of Australian identity.

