#### Sample size

It is aimed to recruit a total of 420 participants (200 intervention/200 information only/20 control). Based on our previous research in the area, it is anticipated that there will be approximately 35% attrition over 4 weeks of follow-up for reasons such as failure to complete follow-up questionnaires. A total sample of approximately 260 (420–140) completing participants (130/group) is required to detect a medium effect in sun-protective behaviour. This sample size was determined by power analysis using the G*Power program [37,38]. Significance level (alpha) was established at 0.05 to avoid a Type 1 error, power (1–beta) was set at 95% to avoid a Type II error, and effect size was determined at .25. Therefore, for a 95% chance of detecting as significant a 4 week difference in sun safe behaviour, approximately 130 participants in each group are needed to complete the study.

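### Two outcomes are primary with no order or success rule, while the single alpha of 0.05 and the sample size cover one test only: behaviour at four weeks

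*Protocol article*

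**What the plan says.** The Abstract (Methods/Design) states: "Primary outcomes are intentions to sun protect and sun-protective behaviour". Outcome measures and Table 1 repeat both as primary, without ranking them.

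The hypothesis, at the end of the Background, expects gains in intentions and behaviour "compared with participants in both an information only and control group (measurement only").

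Data analyses plans a general linear model for each outcome with group, time and their interaction. It names no deciding contrast or visit and does not say how the two primary results combine.

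Alpha appears once, under Sample size: "Significance level (alpha) was established at 0.05 to avoid a Type 1 error". The same paragraph sizes the trial on one outcome, "completing participants (130/group) is required to detect a medium effect in sun-protective behaviour", and on one time, "for a 95% chance of detecting as significant a 4 week difference in sun safe behaviour". Of the effect size it says only that "effect size was determined at .25".

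**The concern.** The choice and number of primary outcomes, and the alpha used for sizing, are protocol-level decisions, and the article makes them. They do not match: two outcomes are primary, but alpha and sample size are set for one test of one of them. Intentions has no sample size basis and no implied time point.

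Without a rule, a significant result on either outcome could be reported as a positive primary finding, and 0.05 then no longer bounds the risk that such a finding is false. The two outcomes also differ in weight. In the article's own theory intention is the proximal determinant of behaviour, and the Discussion places the benefit of the trial in behaviour. Intention is also measured straight after a session in which intervention participants set a goal and write a contract about it. A rise in intention with no change in behaviour is therefore a plausible result, and the article does not say whether it would count as success.

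**Working it through.** **Inputs from the article.** Two primary outcomes; alpha 0.05; power 95%; effect size .25, called medium, metric not named; about 260 completers, 130 per group; allocation 200:200:20; attrition about 35%.

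**Assumptions.** Two-sided tests (sidedness is not stated), and a range of correlations between the two primary test statistics.

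**1. The plan's own figure.** G*Power's one-way ANOVA uses the noncentral F distribution with λ = f²N. With f = 0.25, alpha 0.05 and 95% power:
- two groups: N = 210 (105 per group); power at 260 is 98.0%
- three equal groups: N = 252 (84 per group); power at 260 is 95.7%

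Neither gives 260 exactly. The figure does equal 400 × 0.65, the expected completers in the two large arms. Read as d = 0.25, the requirement would be 416 per group. The word medium fits f = 0.25, which for two equal groups is d = 2f = 0.5, but the article does not say so.

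**2. How many primary tests.** Data analyses supports at least one group-by-time test per outcome, so two tests is the firm minimum.

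**3. Error if either test suffices.** With independent tests:

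1 − (1 − 0.05)² = 1 − 0.9025 = 0.0975

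With correlated tests, 1 − P(|Z₁| < 1.96 and |Z₂| < 1.96) from the bivariate normal distribution:

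| Correlation | Chance of at least one false positive |
|---|---|
| 0 | 9.75% |
| 0.3 | 9.5% |
| 0.5 | 9.1% |
| 0.7 | 8.3% |
| 0.9 | 7.0% |

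For correlations up to 0.7 this is about 8 to 10%.

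**4. Conditional extension.** If each outcome were also tested pairwise against each comparator, unadjusted, there would be four tests: 1 − 0.95⁴ = 18.5% under independence, and about 13 to 18% in a simulation with a shared intervention arm, 130/130/13 completers and outcome correlations of 0 to 0.9. The article does not describe these tests, so these figures are not a property of the plan as written.

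**5. If success needs everything.** Requiring both outcomes against both comparators does not inflate Type I error. The cost is power: 20 × 0.65 = 13 control completers against 130 gives about 40% power per comparison at d = 0.5.

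**6. Cost of control.** Two-sample t test, 130 per group, noncentrality d√(130/2):

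| Reading of .25 | Noncentrality | Power at 0.05 | Power at 0.025 |
|---|---|---|---|
| f = 0.25 (d = 0.5) | 4.03 | 98.0% | 96.2% |
| d = 0.25 | 2.02 | 52% | 41% |

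**The case against.** The strongest reply is that this is a condensed article. A multiplicity method, the order of contrasts and a success rule are commonly left to the analysis plan, and the article never says that no adjustment will be made. That stands for the detail of any adjustment. It does not remove the mismatch between two declared primaries and a sample size and alpha set for one test. An adjustment added later would also change the alpha that the sample size should have used.

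A second reply is that the hypothesis names intentions and behaviour together and both comparators, so success may require all of them. Type I error would then not be inflated. This is a fair reading, but the article does not state it as a rule, and it would leave power resting on about 13 control completers.

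Several stronger readings are tempting and are not supported:
- A reader might infer that every comparator and visit is tested at 0.05. Data analyses gives no alpha and no pairwise or per-visit tests, and one interaction test per outcome would pool arms and visits.
- A reader might say that there is no primary time point at all. Sample size implies four weeks for behaviour; what is missing is its designation in the outcome and analysis sections, and any time point for intentions.
- A reader might take the phrase about avoiding a Type 1 error as a claim of trial-wide control. It describes the alpha entered in the power calculation.
- A reader might put the immediate rise in intention down to lack of blinding. The article does not discuss blinding, and the information only group has also just finished a session when it completes that survey.

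**Conclusion.** The concern holds for the two primary outcomes. If either alone can carry the claim at 0.05, the false-positive risk is about 8 to 10%, with 9.75% under independence. This assumes two-sided tests, one test per outcome, and a correlation between them of no more than about 0.7; at 0.9 it is 7.0%. Larger error rates depend on unadjusted pairwise or per-visit testing that the article neither states nor rules out, so they should not be charged to the plan. If all results were required for success there would be no inflation, but power against control would be about 40% even at d = 0.5. Either way, the protocol needs a stated rule.

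**What to change.** **Preferred.** Name the test already powered as the single primary test: behaviour at one month, intervention against information only, alpha 0.05. Test intention at one month second, in fixed sequence, for the same contrast. Treat the contrasts against the 20-person control arm as supportive. The first test loses no power. The price is that intention becomes confirmatory only if behaviour is significant, which demotes a stated co-primary outcome.

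**Alternative.** Keep both outcomes primary and apply Holm to intervention against information only at one month. The smaller p-value must then meet 0.025 and, if it does, the larger is tested at 0.05. With 130 completers per group, power at 0.025 is about 96% if .25 is Cohen's f, and about 41% if it is d.

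**In either case.** State the effect size metric under Sample size, because the cost of the Holm option, and the adequacy of 130 per group even at 0.05 (98% or 52%), depends on it. Under the f reading the change is to the text only and needs no further participants. Under the d reading the sample size itself would need to be revisited.

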**Discussion:**

The study will contribute to an understanding of the effectiveness of a TPB-based online intervention to improve Australian adults’ sun-protective behaviour.

**Trials registry:**

Australian and New Zealand Trials Registry number ACTRN12613000470796

## Background

Australians represent a high-risk group for the development of skin cancer, living in a country which has the joint highest incidence of skin cancer in the world [1], with two out of three Australians expected to develop skin cancer by the age of 70 years [2]. Melanoma and non-melanoma skin cancer combined account for approximately 80% of all new cancers diagnosed in Australia every year [3]. Specifically, incidence and mortality rates for melanoma in Australia are the highest in the world, with over 11,500 new cases diagnosed in Australia in 2009, including 3,000 people in the state of Queensland. Melanoma of the skin is the third most commonly diagnosed cancer in both Australian males and females (excluding non-melanoma skin cancer), with incidence rates continually increasing over the previous 3 decades [1]. This trend is illustrated by an increase of 42% in the melanoma incidence rate for males and an increase in the melanoma incidence rate of 18% for females between 1991 and 2009 [1]. Because of its high incidence, non-melanoma skin cancer (NMSC) also represents a significant burden on the Australian health budget. NMSC accounted for 950,000 general practitioner consultations in 2007 [4] and was listed as the most common reason for hospitalisation with the principal diagnosis of cancer in 2010-2011, with 95,312 people hospitalised [1].

Exposure of the skin to ultraviolet radiation [5,6] accounts for 95 to 99% of skin cancer diagnoses in Australia [3]. Most skin cancers are preventable by encouraging consistent use of sun protection methods including using a broad spectrum water resistant sun protection factor (SPF) 30+ sunscreen, staying in shady areas and limiting time in the sun between 10 am and 3 pm, and wearing a wide brimmed hat, sunglasses, and protective clothing to reduce sun exposure and sunburn [7].

Despite the potential of sun-protective behaviours to prevent skin cancer, the most recent data show that the majority of Australian adults are failing to adopt sun-protective behaviours [8-10]. The 2010-2011 National Sun Protection Survey found that only 19% of adults wore clothing with longer arm-cover during periods of peak sun exposure, 37% of adults used sunscreen, and 45% wore hats [11]. Wearing sunglasses was the most commonly adopted sun-protective behaviour among adults with 57% use. Exposure to the sun resulting in sunburn over the preceding weekend was reported by 13% of adults in this survey. A further study examining the incidence of sunburn among adults in the state of Queensland over the summer months found one in eight men and one in 12 women in Queensland reported being sunburnt on the previous weekend [12].

The human and economic burden of skin cancer in Australia provides an important impetus for research that informs health promotion interventions. Previous research and health change interventions in the field of adult sun protection has predominantly focused on measuring the adoption of sun-protective behaviour and raising awareness of the health implications of ultraviolet exposure and the means of reducing sun exposure [13]. While knowledge and awareness of risk have significantly increased over the last decade, recent findings suggest that these increases are not currently translating to adequate sun protection, a reduction in incidence of sunburn and skin cancer, or improved attitudes [13,14].

The socio-cognitive factors underpinning adult Australians’ decision-making about sun-safe practices have not yet been fully established [8] and the existing research falls short of providing a comprehensive model to address the complexity of behaviour change and to fully understand the motivations behind adults’ sun-protective decision-making. Understanding Australians’ sun-protective behaviour decision-making is critical to the development of theory-based interventions to increase sun-protective behaviour and effectively halt the trend in increasing incidence of skin cancer in Australia. The Theory of Planned Behaviour (TPB; [15]) offers a model of behaviour prediction useful not only in understanding sun protection decision-making but also in informing intervention development.

### Theoretical framework

The TPB [15] is a well-validated decision-making model that has been used to successfully understand a range of social and health-related behaviours [16-22]. Specifically, the effectiveness of the model’s application to predicting and understanding sun-protective behaviour has been demonstrated in Australia [18,20,23,24] and internationally [17,19]. In the model (see Figure 1), behavioural intention is the most proximal determinant of the target behaviour. Attitudes (positive and negative behavioural evaluations), subjective norms (perceived pressure from important referents to perform the behaviour), and perceived behavioural control (PBC; perceptions of control over performing the behaviour/perceived ease or difficulty in performing the behaviour), in turn, exert an impact on behaviour via behavioural intention. PBC is also conceptualised as a direct predictor of behaviour [15]. The underlying cognitive belief-base of attitudes, subjective norms, and PBC are behavioural (costs and benefits), normative (specific referents’ approval or disapproval), and control (barriers and facilitators) beliefs, respectively. The relative strength of the predictors in the model are expected to vary depending on the behaviour under study; based on 185 applications of the TPB across a range of behaviours [25], attitudes, subjective norms, and PBC together explained an average of 39% of the variance in intention, with intention accounting for an average of 27% of the variance in behaviour (and a further 2% of variance attributable to PBC).

**Figure 1 F1:**
[figure not shown]
**The theory of planned behaviour (TPB) **[15]**.**

Ajzen [15] describes the TPB as a model open to the inclusion of additional predictors provided that there is strong theoretical justification for their inclusion and that the predictors explain an adequate amount of unique variance. Accordingly, extensions to the TPB have been proposed to make the model applicable in a range of different contexts but, also, to address conceptual and measurement issues with the relatively weak normative construct. Subjective norm is repeatedly found to be the weakest predictor of intention [25], which has led some researchers to propose a re-conceptualisation of this construct or extensions to the TPB to incorporate other normative influences. In the sun safety literature, researchers have suggested broadening the normative component of the model with the addition of group norms [23,26], image norms [16], and personal norms [27]. Informed by a social identity [28] and self-categorisation approach [29], group norms aim to capture the perceived expectations and actions of members of specific, salient, in-groups. The in-group that is salient for a particular behaviour is situation-specific and will, as such, vary across contexts. Group norma reflect a *prescriptive* rather than a *descriptive* normative influence and comprise two components: behavioural norms, which are the perception of whether group members perform the behaviour, and group attitudes, which are the perception of group members’ evaluation of the behaviour. In the TPB, a behaviour that is typically performed and highly valued by members of a salient in-group is, thus, thought to strengthen behavioural intentions. Extended TPB models that have incorporated group norms have received recurring support in the literature (e.g., [23,30,31]). In the context of sun safety, White et al. [20] found that the perceived group norms of friends had a direct influence on young Australians’ sun-protective intentions and behaviour.

Image norms are another normative influence potentially relevant to people’s sun-protective intentions and behaviour [16]. These norms are the cognitive representations of stereotypical members of particular groups (e.g., tanned and non-tanned people), and reflect individuals’ self-presentational concerns about their image [16]. For instance, perceptions that a tan is attractive and healthy might lead individuals to deliberately expose themselves to the sun without using sun protection to develop a tan. Image norms are thought to represent the values of society in general (e.g., as portrayed in the media). Previous attempts to modify image norms have focused on altering normative perceptions about the attractiveness of being tanned [16]. Jackson and Aiken [32] also suggest that increasing the perceived attractiveness of pale image norms may assist in improving sun-protective behaviours.

The concept of personal norms has also been proposed as an addition to the normative component of the TPB (e.g., [15]). Personal norms are regarded as an individual’s own values as they relate to performing a certain behaviour [33]. While the performance of some behaviours may be linked to moral or ethical values (i.e., moral norms), self-identity can also influence the formation of personal norms. For instance, while individuals may not feel any moral obligation to perform sun-protective behaviours, they may regard themselves as a responsible person and, therefore, engage in behaviours which are perceived to reduce risk (i.e., sun safety, avoidance of sunburn). Personal norms differ from self-identity, however, in that it originates more from personal rather than societal values [33].

To target influential determinants of sun protection intentions and behaviour, this online intervention builds on two previous studies undertaken by the authors. A qualitative elicitation study (N = 42) ([name], [name], [name], [name]: A qualitative exploration of sun safety beliefs among Australian adults, forthcoming) was conducted to identify relevant costs and benefits of sun protection, important referent groups, and barriers and facilitators to sun protection. The findings of the qualitative study were then used to develop measures for a large-scale prospective study (N = 579) to assess the relative predictive utility of the TPB predictors and additional social, personal, and normative influences on Australian adults’ sun-protective behaviour ([name], [name], [name], [name], [name], [name]: Predicting Australian adults’ sun-safe behaviour: Examining the role of personal and social norms, submitted).

Critical beliefs influencing sun protection identified by the authors in previous research informed the development of the current intervention. Hamilton et al. [24] found people were more likely to sun protect if they believed long-sleeved shirts and hats were fashionable, were influenced by friends’ favourable attitudes towards sun protection, and believed they were less likely to tan if practising sun protection. Further, predictors of non-adoption of sun-protective behaviours which will be incorporated into this study are the perception that sun protection was inconvenient and easy to forget. Additional influences identified based on qualitative data have been incorporated into the intervention, namely the role of personal choice/responsibility in the decision to engage in sun-protective behaviour and the belief that being in the sun and having a tan are part of Australian identity and culture.

Computer-based interventions have been used to target behaviour change in a wide range of health issues over the last decade and provide a means of administering economical and easily accessible interactive health interventions which are far reaching within the population [13,34]. Research by Cugelman et al. [34] found that, compared with waitlists, online interventions have demonstrated moderate efficacy while, compared with print materials, they offer similar impacts but with the advantages of lower costs and broader reach. Further, research by Webb et al. [35] found that more extensive use of theory, and specifically online interventions based on the TPB, tended to have more substantial effects on behaviour. Despite their demonstrated efficacy in producing health behaviour change, online, multi-behavioural, theory-based interventions have yet to be explored fully as a medium to target adults’ sun-protective attitudes, beliefs, and sun-protective behaviour within the Australian context.

Limited research has examined the efficacy of online/web-based interventions in increasing a specific sun-protective behaviour (e.g., sunscreen use; [36]); however, there is a particular dearth of theory-based, online interventions targeting multiple sun-protective behaviours. We hypothesise that adults exposed to the online intervention will report an increase in positive sun-protective attitudes, normative support, and self-perceptions of control/self-efficacy, leading to increased sun protection intentions and behaviour, compared with participants in both an information only and control group (measurement only).

This paper presents the study protocol for an online intervention aimed at improving sun-protective behaviour in adults. The research will use an extended version of the TPB to develop and test the efficacy of an online sun-protective intervention derived from this approach. The intervention will target previously identified attitudes toward sun protection, normative influences, and barriers and motivators, as well as targeted aspects of personal choice/responsibility, and tanning being part of Australian identity.

